## Methods and Design

### a) The scientific design of the study

#### *The survey objectives*

This research project is aimed to:

- conduct a cross-sectional observational, non-interventional, internet survey in consenting 18+ year-old LGBTI participants using an anonymous web-based self-administered questionnaire without any geographical restrictions;
- examine correlates of HIV infection to understand how survey variables, such as demographic, economic, socioecological, homophobic, psychosocial, attitudinal and behavioural, potentiate HIV risk behaviour and access to and uptake of HIV care and treatment services;
- provide evidence in favour of more LGBTI-inclusive health and HIV service delivery, advocacy, and policymaking.

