  - currently on antiretroviral therapy

- discussed pre-exposure prophylaxis
- use of pre-exposure prophylaxis
- health-care stigma

The consensus questionnaire (see [appendix 1](#)) consists of three modules:

- 1st module for LGBTI people, comprising 45 questions;
- 2nd module for MSM and transgender people, comprising 15 questions;
- 3rd module on HIV stigma, comprising 22 questions.

It was our preference to start and finish the survey with relatively comforting questions and statements to reduce any unforeseen discomfort in the participants.

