#### c) Sampling strategy, recruitment and voluntary informed consent

The target population of the survey are 18+ year-old LGBTI people. The survey can be accessed using a web [link](#) that will be provided at LGBTI social networks, e.g. the LGBT Foundation social networks, as well as national and regional LGBTI community networks. The survey will be opened for a duration of 3 months. Recruitment will not involve any direct recruitment and is anonymized. Participation in the survey is not incentivised. We are aware of the limitations associated to these voluntary recruitment channels and we are exploring, with LGBTI civil society organisations and UNAIDS teams at country and regional levels, all additional opportunities that could increase the participation of marginalised or remote communities and individuals.

It was considered that participants who are afraid to share information about risk behaviours or HIV status may drop out of the survey or falsify their responses. To successfully survey LGBTI people, these biases are being minimized by obtaining fully informed voluntary consent at the start of the survey from participants and ensuring their absolute confidentiality.

The informed consent of voluntary participants is summarised at the introduction of the survey and the following information is provided through a link:

- a concise description of the survey and the organization conducting it, the survey objectives, the populations being invited to participate;
- a clear indication that participation is voluntary and that participants have the right of withdrawal from the survey at any time, or skip any sensitive question/s;
- a description of the participant's role in the survey, including duration of participation, the general nature of the questions;
- a description of the possible discomforts of participation;
- a description of the benefits to the community that are expected to come from the survey
- a description of how the findings will be made available to the respondents and the LGBTI community
- measures made to protect the privacy and confidentiality of the participant and any information that the person provides;
- documentation that the protocol was reviewed and approved by Research Ethics Review Committee (*to be completed once WHO ERC approval*);
- how the results of the survey will be used. This includes explicitly the possible use of the data for scholar purpose, such as doctoral or post-doctoral productions by the research team

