## I) Sample size

Various population size estimate of the different LGBTI groups are available of most low- and middle-income countries. The present survey does not pretend to collect a statistically representative sampling of these population groups. The modelling, analyses and findings of this survey will be careful in extrapolating conclusions to the entire population groups of a said country. Rather, we would like to provide statistically robust modelling of the correlates of HIV infection of the participants to the survey. This is in line with current practice in surveillance for key populations as it does not aim at a nationally representative sample of a country's population.

We set the minimum *a priori* sample size of 100 respondents per country studied, corresponding to a 0.10 (.90) probability level for a five predictors multiple regression.

The sample size for multiple regressions will vary for each equation in our model. For example, for an anticipated effect size ( $f^2$ ) = 0.15, a desired statistical power level of 0.90 and a probability level of 0.05 (0.95), a regression with five predictors would require a sample size of 116 respondents.

We study the combination of answers at the level of the individuals. Missing data can be estimated with multiple imputations. We use polychoric matrices for ordinal and categorical data. Multiple choice questions will be treated on a case by case basis. Detailed description of statistical methods will be provided with findings.

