27. Have you ever heard **verbal insults** directed at you because someone knew or presumed your sexual orientation or your gender identity? If yes, when was the last time?

- ☐ no, never
- ☐ yes, within the last 12 months
- ☐ yes, more than 12 months ago

28. Have you ever been **physically assaulted** because someone knew or presumed your sexual orientation or your gender identity? If yes, when was the last time?

- ☐ no, never
- ☐ yes, within the last 12 months
- ☐ yes, more than 12 months ago

*[sub-section on access to healthcare services]*

29. When did you last have an HIV test?

- ☐ within the last 6 months
- ☐ within the last 12 months
- ☐ more than 12 months ago
- ☐ never

30. In the last 12 months, have you avoided going to or delayed going to a health care facility for sexual health or for HIV-related services? (tick as many as apply)

- ☐ would be too risky for me
- ☐ I can't pay
- ☐ I'm embarrassed
- ☐ last time I felt stigmatised
- ☐ I'm worried someone may learn about my sexual orientation
- ☐ it's not convenient (transport, time, distance)
- ☐ I could not find the times
- ☐ it was not important to me
- ☐ I did not avoid or delay my health consultation
- ☐ other

31. Did you experience any of the following the last time you went to a health facility (tick as many as apply)

- ☐ I felt welcomed
- ☐ I had no negative experience

- ☐ verbal abuse (yelling, scolding, name calling, ...)
- ☐ physical abuse (pushing, hitting, physically hurt...)
- ☐ was given a condition (requirement) to change my sexual behaviour prior to treatment
- ☐ was given a condition (requirement) to change to change my gender identity prior to treatment
- ☐ refused to help me
- ☐ other

*[sub-section on stigma & discrimination at workplace]*

32. In the last 12 months, have you experienced any of the following at your current work or when you applied for a job? (tick as many as apply)

- ☐ I faced no discrimination
- ☐ my application was refused because I am gay, bi, lesbian, trans
- ☐ I was harassed or ridiculed at the workplace
- ☐ I was not promoted because I am gay, bi, lesbian, trans
- ☐ I was told not to show me being gay, bi, lesbian, trans
- ☐ I was denied certain work-related benefits because I am gay, bi, lesbian, trans
- ☐ I was told not to work with clients
- ☐ I'm not working
- ☐ I didn't apply because I'm gay, bi, lesbian, trans
- ☐ other

33. At work, do you earn less than your nearest heterosexual (straight) counterpart who does the same kind of work

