- ☐ yes
- ☐ no
- ☐ don't know
- ☐ does not apply

*[Section on quality of sex]*

34. Over the past three months, how satisfied are you with the quality of your sexual life?

- ☐ 10 really satisfied
- ☐ 9
- ☐ 8
- ☐ 7
- ☐ 6
- ☐ 5
- ☐ 4
- ☐ 3
- ☐ 2
- ☐ 1 really not satisfied

35. I would like to have sex

- ☐ a lot more often
- ☐ a little more often
- ☐ I have enough sex as is
- ☐ a little less often
- ☐ a lot less often

*[Section on sociodemographic data]*

36. Your relationship situation

- ☐ single
- ☐ in a relationship with a man
- ☐ in a relation with a transgender person
- ☐ in a relationship with a woman
- ☐ both with a man and a woman
- ☐ I don't know

37. Education (highest degree completed):

- ☐ none
- ☐ primary school
- ☐ secondary /high school
- ☐ university first degree
- ☐ masters/doctorate

38. Current employment status:

- ☐ employed
- ☐ self-employed
- ☐ doing casual or part-time work
- ☐ unemployed
- ☐ student
- ☐ retired
- ☐ other

*[Section on economic situation]*

39. Which comes closest to your feelings about your income these days?

- ☐ living really comfortably on present income
- ☐ living comfortably on present income
- ☐ neither comfortable nor struggling on present income
- ☐ struggling on present income
- ☐ really struggling on present income

40. Considering all debts or loans of whatever type, were you behind with payments by more than 3 months at any time during the last 12 months?

- ☐ never
- ☐ rarely
- ☐ occasionally
- ☐ most of the time
- ☐ all the time
- ☐ does not apply

41. How often have there been times in your life when you have lived in poverty by the standards of that time?

- ☐ never
- ☐ rarely
- ☐ occasionally
- ☐ most of the time

*[Section on social situation]*

42. Think of a ladder representing where people stand in **your country**

At the **top** of the ladder are the people who are the **best off**. At the **bottom** are the people who are the **worst off**. Where would you place yourself on this ladder at this moment?

- ☐ 10 among those having most money, most education and

- most respected jobs
- ☐ 9
  - ☐ 8
  - ☐ 7
  - ☐ 6
  - ☐ 5
  - ☐ 4
  - ☐ 3
  - ☐ 2
  - ☐ 1 among those having the least money, least education and least respected jobs or no job

43. Now, think of a ladder representing where people stand in your **local community**

Where would you place yourself on this ladder at this moment?

- ☐ 10 highest social standing in my community
- ☐ 9
- ☐ 8
- ☐ 7
- ☐ 6
- ☐ 5
- ☐ 4
- ☐ 3
- ☐ 2

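### Q30 has no answer for respondents who needed no sexual-health or HIV care, so avoidance among people who needed care cannot be identified from it

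*Protocol*

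**What the plan says.** Q30 stands in the access-to-healthcare part of the Appendix 1 questionnaire. It asks, over 12 months, "have you avoided going to or delayed going to a health care facility for sexual health or for HIV-related services", and respondents may tick several answers. The list holds eight reasons, among them "it was not important to me". It also holds one negative answer, "I did not avoid or delay my health consultation", and an other category.

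The item belongs to the first module, described under Questionnaire development as the "module for LGBTI people, comprising 45 questions". No filter or routing comes before it. The first routing follows Q45: respondents who answer lesbian or straight go directly to Q61 and miss module 2.

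Elsewhere the questionnaire does provide for people whom a question does not concern. Q33 and Q40 in the same module offer "does not apply", Q4 and Q46 to Q48 have an equivalent, and Q32 has an answer for people who are not working.

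Section c) tells participants that they may withdraw "or skip any sensitive question/s". The sample size section says "Multiple choice questions will be treated on a case by case basis" and allows multiple imputation of missing data. Among the survey objectives is to understand how the survey variables relate to "access to and uptake of HIV care and treatment services".

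**The concern.** A person can avoid or delay care only if there was care to seek. Q30 does not record whether there was. Its one negative answer reads as though a consultation had been due, and the reason about importance can mean either low priority or no need. Three kinds of respondent (no need, needed and went, needed and avoided) are thus collected in answers that separate only two.

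Q30 is the only item put to everyone about avoided or delayed sexual-health or HIV care, and it carries the stigma, cost and disclosure reasons. If need differs between groups or countries, a difference in Q30 answers may partly be a difference in need. The protocol plans country dashboards of key indicators and sees this round as a possible baseline for later ones, so an ambiguity built in now could carry forward.

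**Working it through.** The protocol states no avoidance rate, numerator or denominator for Q30, so there is no figure to reproduce. The check has two parts.

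**1. Can need be recovered from other items?**

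- Q29 dates the last HIV test. It shows some attendance for testing, but an untested person may or may not have needed care, and it says nothing on other sexual-health needs.
- Q31 concerns the last visit to any health facility, with no time window and no service named.
- The exposure items that might stand in for need (Q46 to Q53) are in module 2, which lesbian and straight respondents do not see.
- A skipped Q30 is an unexplained blank. It could come from no need, discomfort or anything else, and it may be imputed.

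No item or combination of items asked of everyone gives need. A later analysis plan can choose a denominator but cannot create an answer that was not collected.

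**2. How far could the measured rate move?**

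Inputs, all assumed because the documents give none:

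- *a*, avoidance among people with need: 20% or 40%
- *q*, share of respondents with no need: 10%, 30% or 50%
- *r*, share of no-need respondents who tick a reason or other and are counted as avoiders: 0% to 100%

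For a simple rate among all who answer, with the rest of the no-need group ticking that they did not avoid care:

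measured = *a*(1 − *q*) + *q·r*, and so measured − *a* = *q*(*r* − *a*).

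With *a* = 20% and *q* = 30%:

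- *r* = 0%: 0.20 × 0.70 = 14% (14/20 = 0.70, 30% too low in relative terms)
- *r* = 10%: 14% + 0.30 × 0.10 = 17%
- *r* = 50%: 14% + 0.30 × 0.50 = 29% (29/20 = 1.45, 45% too high)
- *r* = 100%: 14% + 30% = 44%

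Over the wider range:

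| *a* | *q* | *r* = 0% | *r* = 50% | *r* = 100% |
|---|---|---|---|---|
| 20% | 10% | 18% | 23% | 28% |
| 20% | 30% | 14% | 29% | 44% |
| 20% | 50% | 10% | 35% | 60% |
| 40% | 10% | 36% | 41% | 46% |
| 40% | 30% | 28% | 43% | 58% |
| 40% | 50% | 20% | 45% | 70% |

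The error is negative when *r* is below *a*, zero when they are equal, and positive when *r* is above *a*. If every no-need respondent skips the item and blanks are left out, the measured rate equals *a*. Neither the sign nor the size can be learned from the data that Q30 collects.

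**The case against.** **The protocol defines no rate.** A reader might infer that the avoidance rate will be divided by everyone, including people who could not have avoided care. The document does not say so. It defers multiple-choice items to case-by-case treatment, and coding and denominators commonly belong to the analysis plan, which is not at hand. This stands: the choice of denominator is not the finding. The missing answer is, because it limits every denominator that could be chosen.

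**People without need do have an answer.** Saying that they did not avoid or delay care is literally true for them. They may also tick other, or leave the item blank, since consent is the only question marked mandatory. This stands too. The defect is that different groups share one answer, not that anyone is left without one.

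**A false group difference is not shown.** A reader might infer that Q30 would produce a spurious twofold gap between, say, gay and lesbian respondents. With 25% avoidance among those with need in both groups, and need of 80% and 40%, the item gives 0.80 × 0.25 = 20% against 0.40 × 0.25 = 10%. Those need shares have no basis in the documents, and the result requires every no-need respondent to tick that they did not avoid care. If half tick a reason instead, the figures are 20% + 0.20 × 0.50 = 30% and 10% + 0.60 × 0.50 = 40%, and the gap reverses. The protocol plans no such contrast on Q30.

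**The all-respondent share is legitimate.** If labelled as such, it is a valid description. Stated lack of need may itself be shaped by stigma, so removing those people could remove real avoiders. This stands, and it is why a rate restricted to people with need should be shown beside the all-respondent rate and not replace it.

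**Q30 is one item of 82.** Neither of the first two research questions names it, access and uptake are also covered by Q29, Q31, Q80 and Q81, and the dashboards are not said to use it. That limits the weight of the point but does not make the item interpretable.

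**Conclusion.** The point holds as a limit of the questionnaire. Q30 goes to all module 1 respondents without a need filter or a not-needed answer, so people without need cannot be told apart from those who needed care and went, or from those who avoided it. Avoidance among people needing care is not identifiable, and comparisons between groups or countries may partly reflect need.

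The bias may go either way and its size is unknown. The range of 14% to 29% around a true 20% rests on three assumptions: 20% avoidance among those with need, 30% of respondents without need, and 0% to 50% of these ticking the not-important reason while the rest tick that they did not avoid care. It shows the sensitivity and is not an estimate. The point affects one access item and does not touch the first two research questions as stated. It deserves correction because it can be corrected only before the answers are collected.

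**What to change.** Before launch, add one option to Q30: *I did not need these services in the last 12 months*. Make it exclusive, so that it cannot be ticked together with a reason. Report avoidance twice, among all respondents and with the no-need group left out, and give the no-need share by group beside both.

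The cost is one line to be translated and back-translated into the 16 languages other than English listed under Languages and translations, plus a small change in the survey tool. No question is added, so the questionnaire stays as short as its stated principles ask.

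There are two downsides. Some people who avoided care may declare that they had no need; the reported share shows how large that group could be but does not correct for it. The item would also depart slightly from any version used in other surveys; merging the new option with the did-not-avoid answer approximates the present form for comparison.

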**(Thank you message)**

*Thank you very much for your support.*

*Sign up to get the results of this study and participate in future studies, your information is completely anonymous, any IP address is decoupled, encrypted and deleted at the end of the study. [https://lgbt-token.org/research\\_signup](https://lgbt-token.org/research_signup) You may share the survey via: <https://www.research.net/r/LGBTHappinessResearch>*

*Get tested for HIV regularly. For more information: <https://hornet.com/about/know-your-status/>*

(Only participant who answered I'm HIV positive are offered to participate to module 3 below)

exit

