### *Questionnaire development*

The questionnaire of the survey contains established instruments for collecting survey data among key populations, such as LGBTI people, using validated questions and scores. These instruments include questions that have been used throughout the world; thus, their continued use will enable researchers to compare survey results across countries. The standardized instruments provided with these guidelines were designed to be self-administered using electronic or web-based data collection methods.

The questionnaire was built on the following four principles:

1. The process must preserve the complete anonymity of respondents. The privacy and security of respondents must be ensured at every step of the survey;
2. Questionnaire should be as short as possible. Only questions that are necessary should be included;
3. Filling out the online questionnaire should expose participants to no more than minimal risk, such as minimal discomfort, minimal anxiety;
4. Questions selected should have their reliability and validity already demonstrated and their collection should enable triangulation with other surveys.

We followed the following **key steps in questionnaire development**:

- decided on methods for questionnaire administration;
- determined investigation topics (questionnaire domains);
- developed and adapted the questionnaire;
- conducted cognitive testing;
- pre-tested the questionnaire;
- pilot tested the survey tool.

The content of the questionnaire is harmonized with standard indicators and protocol checklists used in behavioural surveillance. The questionnaire is organised as modules focused on topics, such as:

- demographics
- time preference, risk aversion
- socioeconomic status, including a question on financing hormones for transgender people
- behaviours increasing vulnerability to HIV infection (e.g. unprotected receptive anal intercourse, buying sex, selling sex, sharing nonsterile injecting equipment, alcohol and drug use)
- stigma and discrimination in the community, at workplace and health facility (sexual orientation, gender identity, HIV)
- internalized homophobia
- violence
- general health status
- mental health, including depression
- social support network, including family
- HIV prevalence, access to HIV and other health services, HIV services uptake:
  - knowledge of serostatus
  - eligible but not on HIV treatment
  - viral load suppression
  - unsuppressed viral load
  - currently in care

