#### h) Vulnerability to harm or to risk of exploitation

The survey does not imply any person-to-person contact. It does not collect any personal information and records are unidentifiable. The questions, taken all together, do not reveal any information that could make respondents vulnerable to harm or to risk of exploitation. The questionnaire does not use or collect geolocation data, it does not install any tracker cookies on the device of the respondents. We anticipate no harm or risk of exploitation.

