#### i) Steps that will be taken to minimise the risks to participants, including confidentiality and privacy

As described in the section above, the online questionnaire should not entail no more than minimal risk in terms of potential stress and/or anxiety while responding to the questionnaire. The online

questionnaire compiles questions previously used in other surveys and, to the best of our knowledge, do not have any physical risk.

The data privacy and protection of information obtained from participants is important for this survey. To protect the anonymity and data privacy of the participants, the following steps have been taken:

- The study is made available to LGBTI population through a secure, SSL encrypted connection link
- The link does not require any personal identifier, email, phone or person-to-person contact
- Data in transit (ex: while responding online) are encrypted using secure TLS cryptographic protocols
- The collection tool, Survey Monkey, has [certified its compliance](#) with the EU-U.S. Privacy Shield Framework (GDPR) and Swiss-U.S. Privacy Shield
- The questionnaire does not collect any personal information. Questions, even taken all together, do not reveal any information that could enable to identify the respondents or his/her geolocation
- The collection tool does not install any targeting or advertising cookies
- IP addresses are instantly decoupled from the questionnaire, encrypted and deleted at the end of the online survey (3 months) by the survey tool
- Data records are unidentifiable

We have, to the best of our knowledge, taken all the measures to prevent any identification of the respondents by the research team as well as by any authority.

We believe we have taken all the necessary steps to ensure data privacy and to protect the confidentiality of information obtained from participants, and to protect them from social or economic discrimination or stigmatization following their participation to the online questionnaire.

Furthermore, as mentioned above, a mailbox representing the participating agencies will be provided to address any query and/or event related to this survey.

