#### o) Any information that will be provided to participants following their participation

The following elements are provided to respondents before they leave the survey:

- A thank you message for their participation and reminder of the anonymity of the survey;
- A weblink to the LGBTI Foundation where additional information on the survey, periodical updates, the general findings and next steps will be provided;
- An advocacy message encouraging participants to get tested for HIV infection.

The survey being anonymous, and the IP addresses being decoupled and encrypted automatically during the time the survey is online (3 months), there is no possibility to provide further direct information to participants after their completion of the questionnaire.

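### The closing page promises complete anonymity in the same sentence as a sign-up whose data handling the protocol does not describe, and section (o) says no such later contact is possible

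*Protocol*

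**What the plan says.** The closing screen, headed as the thank-you message in Appendix 1, reads: "Sign up to get the results of this study and participate in future studies, your information is completely anonymous". The sentence continues with the ground for that promise: "any IP address is decoupled, encrypted and deleted at the end of the study". It then gives a sign-up link on an lgbt-token.org address. The survey link on the same screen is on research.net. The end of module 3 refers back to this message, so HIV-positive respondents who finish that module see it too.

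The body of the protocol describes the closing page differently. Section (o) lists a thank-you with a reminder of the survey's anonymity, a message encouraging HIV testing, and "A weblink to the LGBTI Foundation where additional information on the survey, periodical updates, the general findings and next steps will be provided". It mentions no sign-up. It goes on to say that, because the survey is anonymous and IP addresses are decoupled and encrypted, "there is no possibility to provide further direct information to participants after their completion of the questionnaire".

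The privacy case rests on anonymity throughout. The first principle under Questionnaire development is "The process must preserve the complete anonymity of respondents". Section (h) says of the survey: "It does not collect any personal information and records are unidentifiable". Section (i) says of the survey link: "The link does not require any personal identifier, email, phone or person-to-person contact".

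**The concern.** Respondents are asked to join something that will bring them results and invitations to further studies, and are told in the same sentence that their information is completely anonymous. Some route back to the person is ordinarily needed for that. The safeguard offered, IP handling by the survey tool, does not act on an email address or any other contact detail that a person types into a different site.

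The protocol itself explains why this matters. The rationale refers to policies that criminalise behaviours of high-risk populations, section (g) makes the safety and data security of respondents a top priority, and recruitment has no geographical restriction. Having taken part in an LGBTI survey can be sensitive information in itself, even if no answer is ever attached to it. Someone deciding whether to leave a contact detail should be able to rely on what the screen says.

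**Working it through.** No arithmetic applies: the protocol gives no figure on this point, and none is needed. The check compares the closing screen with the sections that describe privacy and follow-up.

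1. **What the anonymity statement covers on screen.** The invitation and the promise are joined by a comma, with the sign-up address directly after. A respondent would naturally take the promise to include the sign-up.

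2. **What supports the promise.** Only "any IP address is decoupled, encrypted and deleted at the end of the study". Section (i) gives this as a property of the survey tool: addresses are decoupled from the questionnaire, encrypted, and deleted after the three-month survey. Nothing visible extends it to the sign-up site. If it did extend there, it would still concern IP addresses and not what a person enters on a form.

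3. **Whether the sign-up is described elsewhere.** The subsection on data analysis, use and dissemination covers storage, access control and sharing of survey data. Section (i) covers encryption and collection in the survey. Section (k) covers withdrawal of survey records. None of them mentions sign-up data. The sign-up domain also differs from the website that the data management subsection gives for the foundation.

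4. **Whether the closing screen agrees with section (o).** Section (o) offers a weblink that the respondent may visit, and says further direct information cannot be provided. Appendix 1 offers a sign-up to get results and take part in future studies. The first is a page to visit; the second implies a channel back to the person. As written, the two do not describe the same closing page.

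5. **Whether sections (h) and (i) are contradicted.** Strictly, no. The statement in (h) is about the survey, and those in (i) are about the survey link and the questionnaire. A voluntary page on another site makes none of them false. They are incomplete, because they set out the project's privacy measures without the one place where respondents are invited to sign up.

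The direct conflict is therefore between the closing screen and section (o). The unsupported statement is the anonymity promise as it applies to the sign-up.

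**The case against.** The best defence is that the anonymity clause is the reminder of survey anonymity that section (o) plans, badly punctuated. Its IP wording echoes the survey safeguard in section (i), so it may never have been meant to describe the sign-up. Likewise, the sentence in section (o) can be read as saying only that the team cannot reach people from the survey records, which stays true if some respondents volunteer a contact elsewhere. Both readings are plausible accounts of intent. Neither repairs the text: the respondent sees one sentence, and section (o) neither lists the sign-up nor makes an exception for it.

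The defence is right to resist several stronger inferences that a reader might draw:

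- **That the main protection against disclosure fails.** This is not shown. Section (c) relies on consent at the start and on confidentiality of the answers. The sign-up is optional, is offered after the answers are submitted, and sits at a separate address.
- **That the list is a register of named respondents.** The form is not in the document. A contact route is a fair inference; names are not, and a pseudonymous or disposable contact is possible.
- **That sign-up and submission times would link people to their answers.** No section says that either system keeps times, that one party holds both, or that they could be matched. The visible text neither shows such a link nor rules it out.

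One caution also stands. The linked consent information is only summarised, and the Declaration of Confidentiality appendix is not among the pages available. The absence of handling rules can be stated only for the visible text.

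**Conclusion.** The point holds as a defect in participant-facing text. The closing page extends a promise of complete anonymity to a sign-up for which the described safeguards do not provide it, and section (o) describes a different closing page. This goes beyond missing detail, because respondents are told something that the described design does not deliver for the sign-up.

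Its size can be given only in terms of exposure. Everyone who clicks DONE sees the sentence. The document gives no expected sign-up rate, so the number affected cannot be estimated. There is no effect on sample size, measurement or analysis, and nothing here shows that the survey answers themselves lose their anonymity.

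The conclusion rests on one assumption: sending results or invitations to a person requires some contact detail. If the sign-up form collects nothing by which a person can be reached, the promise could be true, but the page could then not do what it offers.

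**What to change.** Choose one of two routes before launch.

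1. **Drop the sign-up.** Replace the sign-up sentence in the Appendix 1 thank-you message with the static results weblink already described in section (o). The closing page and section (o) then agree, and no contact list arises.

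2. **Keep the sign-up and describe it.** Limit the on-screen anonymity statement to the survey answers. Say on screen that the sign-up is optional, is separate from the survey, and may involve contact details. In the subsection on data analysis, use and dissemination and in section (i), state that the list is kept apart from survey records, with restricted access and a deletion date. Add the sign-up to section (o), and limit its statement about further contact to what can be done from the survey records.

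Either way, check that the linked consent information agrees. The cost is about one sentence on the closing page, its translations, and a few lines of protocol text. The first route may leave fewer contacts for future editions. The loss is limited: the subsection on timing and survey intervals says respondents are not tracked from year to year, and section (o) already delivers the findings by weblink.
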